### Economic analysis

The economic analysis will include a cost-consequence analysis, estimating both the costs (hospitalizations, outpatient visits, emergency visits and antihypertensive drugs) and the potential benefits (e.g. reduced incidence of stroke, myocardial infarction, etc.) in natural units. In addition, we will collect information on Health-Related Quality of Life (HRQOL) through the EQ-5d questionnaire, which will allow us to obtain utilities and therefore perform a cost-utility analysis with the estimated benefits in terms of Quality-Adjusted Life-Years (QALY).

A modeling will be performed to obtain longer-term predictions of the results observed in the trial. The results on which this modeling will be based will be survival, quality of life and costs associated with clinical events. A sensitivity analysis (deterministic and probabilistic) will be performed to analyze the robustness of the results. Key parameters will be modified to determine their impact on results. All analyses will be performed using STATA version 14.

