**Fig. 2 Fig2:**
[figure not shown]
Instructions to patients: “HOW TO ACT ACCORDING TO YOUR BLOOD PRESSURE MEASUREMENTS” in the ADAMPA study. Adapted and modified from: The Colour Coding Chart. Supplementary webappendix in: McManus RJ, Mant J, Bray EP, et al. Telemonitoring and self-management in the control of hypertension (TASMINH2): a randomised controlledtrial. Lancet 2010; published online July 8. DOI:10.1016/S0140-6736(10)60964-6

Subsequently, patients will be given -and trained in the use of- a validated home blood pressure monitor (Omron M3 model HEM-7131-E), as well as the “Intervention group booklet” containing: the patient’s code, the reference arm on which BP is measured, the BP target, general information and basic recommendations for improving BP control, instructions to manage the home blood pressure monitor, how to act according to their BP (Fig. 2) and the “monthly registration sheets” for a six month period in order to register their blood pressure twice a day, once in the morning and once in the evening (for the first seven days of each month) and to register contacts related to their BP (by phone, regular or urgent consultation at the office or hospital consultation) during that follow-up period.

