### Intervention

#### Intervention group

##### Blood pressure self-monitoring

Patients will be trained to perform SMBP by the research team through a validated home blood pressure monitor (Omron model M3 HEM-7131-E). Patients will take their BP in the morning and in the afternoon, every day of the first week of each month. This will be done in the morning, before breakfast and before taking their medication (between 6 am. and 9 am.) and in the evening before dinner and before taking their medication (between 6 pm. and 9 pm.). These measurements will be recorded by the patients for the first seven days of each month on the “monthly registration sheets” located in the “*Intervention group booklet*”. If patients want to monitor their BP during the remaining weeks of the month, it is recommended that they just do so one day a week. Patients are instructed to act according to a table that contains easy-to-follow colour coded action steps. This guideline prompts the patient to contact the GP or visit the health center when BP values are very high or very low. Four or more above target readings in a month will require a change in medication (See Fig. 2).

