### Outcomes

The primary outcome will be the change in mean SBP -mmHg- between baseline and 12 months.

Secondary outcomes will include:Change in mean SBP at 6 and 24 months of follow-up.Change in mean DBP at 6, 12, and 24 months of follow-up.Percentage of patients with SBP < 140 mmHg and DBP < 90 mmHg at 6, 12 and 24 months of follow-up.Quality of life (as measured by EuroQoL-5D) at 6, 12 and 24 months of follow-up.Adherence measured by proportion of days covered (PDC) at 6 and 12 months of follow-up.Persistence, defined as period of continuous use of the corresponding drug from the beginning of the follow-up until its discontinuation at 6 and 12 months of follow-up.Therapeutic inertia (TI), defined as the number of patients whose pharmacological treatment had not been modified, divided by the number of patients not reaching the target values (SBP and/or DBP measurements taken at 6 and 12 months of follow-up), ​​according to the recommendations of the European Society of Hypertension and European Society of Cardiology [19].

Other outcome measures:Changes in lifestyle (smoking, exercise, body weight) at 6, 12, and 24 months compared to these characteristics at baseline.Clinical events: We will assess if any of the following adverse events are present during the follow-up: angina, myocardial infarction, stroke, hypotensive crisis and death.Use of health services for hypertension at 6, 12 and 24 months.Incremental cost per quality-adjusted life year gained in the intervention group compared to the control group.Views and experiences of patients and health professionals on the self-management (SMBP plus self-titration) of hypertension.

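### The stated cost list omits the monitor, the training in its use and any uncounted GP planning time in the self-management arm; if it is used for the cost per QALY, the ratio favours self-management.

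*Protocol article*

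**What the plan says.** Under Economic analysis, the protocol article plans a cost-consequence analysis, "estimating both the costs (hospitalizations, outpatient visits, emergency visits and antihypertensive drugs) and the potential benefits". The benefits in the same sentence are given as examples: "e.g. reduced incidence of stroke, myocardial infarction, etc.) in natural units". A cost-utility analysis is then added. Its benefit side is described (QALYs from EQ-5D utilities), but it has no cost list of its own. For the longer-term model the section says: "The results on which this modeling will be based will be survival, quality of life and costs associated with clinical events".

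The Outcomes section includes, among the other outcome measures, "Incremental cost per quality-adjusted life year gained in the intervention group compared to the control group". Whether the intervention is cost-effective is one of the main research questions.

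On delivery, the text for the intervention group under Participant flow through the study says that "patients will be given -and trained in the use of- a validated home blood pressure monitor". The section on blood pressure self-monitoring adds: "Patients will be trained to perform SMBP by the research team". The GP also sets an individual target and a plan for self-adjustment with each intervention patient.

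**The concern.** The four cost items are consequences of care: hospital stays, outpatient and emergency visits, and blood pressure drugs. The inputs that make self-management possible are not among them. A monitor for each patient and a training session are incurred at the start, in one arm only, whatever happens later. If they are left out, the comparison sets the downstream effects of the programme against usual care without charging the programme for its own equipment and staff time.

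At stake is the answer to a stated research question. The article's Discussion also says that the approach might help the finances of the National Health Service, and a health service adopting the programme would have to find these resources. The long-term model would carry the same gap forward, because the only costs it names are those of clinical events.

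**Working it through.** The plan gives no cost, QALY or cost-effectiveness figure, so there is nothing to reproduce. The check has three steps.

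**Step 1: match each delivery resource to the cost list.**

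| Resource (section of the protocol article) | Arm | Covered by the four cost items? |
|---|---|---|
| Home monitor (Intervention group; Blood pressure self-monitoring) | Intervention only | No |
| Training in home measurement by the research team (same sections) | Intervention only | No |
| GP time for the first target and adjustment plan (Intervention group) | Intervention only | Partly at most; it takes place at the practice and may count as a visit |
| GP appointment and new plan after a self-adjustment (Self-titration) | Intervention only | Probably, as an outpatient visit |
| Higher doses or added drugs (Self-titration) | Mainly a cost of the intervention's effect | Yes, as antihypertensive drugs |
| Booklet with recording sheets, educational advice, baseline research-team appointment, calls at four weeks and 3 months, visits at 6 and 12 months (Control group) | Both | Not listed, but largely cancels |

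The gap is therefore the monitor, the training, and whatever initial GP planning time is not recorded as a visit.

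**Step 2: direction.** Let ΔC be the between-arm difference in the listed costs, c the net unlisted delivery cost per intervention patient (c > 0), ΔQ the difference in QALYs and λ the value placed on one QALY.

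- Ratio from the list as written: ΔC / ΔQ.
- Ratio with delivery cost: (ΔC + c) / ΔQ.
- Understatement of the ratio, for ΔQ > 0: c / ΔQ.
- Net monetary benefit: λΔQ − ΔC as written, λΔQ − ΔC − c with delivery cost. The overstatement is exactly c, whatever ΔQ and λ are.

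The sign does not depend on any assumed value, only on c being positive.

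**Step 3: illustrative size.** Neither c nor ΔQ is in the documents. Both are assumptions here, taken over the same time horizon. Entries are c / ΔQ in EUR per QALY.

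| Assumed c (EUR) | ΔQ = 0.005 | ΔQ = 0.01 | ΔQ = 0.02 | ΔQ = 0.05 |
|---|---|---|---|---|
| 30 | 6,000 | 3,000 | 1,500 | 600 |
| 60 | 12,000 | 6,000 | 3,000 | 1,200 |
| 100 | 20,000 | 10,000 | 5,000 | 2,000 |
| 200 | 40,000 | 20,000 | 10,000 | 4,000 |

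The extremes are 30 / 0.05 = 600 and 200 / 0.005 = 40,000. Because c is mostly a one-off cost, a longer model in which the benefit persists would divide it by more QALYs. The shift at 12 months should not be carried over to the model.

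**The case against.** The strongest reply is that this is a short summary in a journal article. An itemised resource list, unit costs and the costing perspective commonly sit in a fuller document that is not shown, and nothing in the article says that delivery costs are excluded. The four items are also attached to the cost-consequence analysis, while the cost-utility analysis is introduced separately.

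Much of this stands. Applying the list to the cost per QALY is an inference, drawn because no other list is given, and the full protocol may name the missing items. But the article does state a cost set. It marks the benefits in the same sentence as examples and does not mark the costs so. The monitor and the training fit none of the four items. The cost-consequence analysis, to which the list does belong, would be affected in the same direction. The planned sensitivity analysis cannot vary a cost that was never entered.

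A reader might infer more than the documents support:

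- *That the intervention is treated as free.* It is not. Extra drugs are counted, and GP appointments after self-adjustment probably are.
- *That booklets and support calls are omitted costs of one arm.* Controls also receive a booklet with recording sheets and the same scheduled calls, so these largely cancel.
- *That a cost-increasing programme will be reported as cost-saving.* That needs savings on the listed items that are positive and smaller than c. Nothing in the documents shows this.

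**Conclusion.** The point holds in a limited form. Followed as written, the cost list leaves out the home monitor, the training in its use and any uncounted initial GP planning time, all in the intervention arm. If the same list feeds the incremental cost per QALY, incremental cost is understated by c per intervention patient and the ratio by c / ΔQ when ΔQ > 0, always in favour of self-management.

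The direction is firm and the size is not. The illustrative span of about EUR 600 to 40,000 per QALY rests wholly on assumed inputs and shows only that the effect could be small or large. The conclusion also assumes that no fuller document adds these items.

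The primary blood pressure comparison is untouched, and the cost per QALY is neither a primary nor a secondary outcome. The point still deserves correction, because it bears on a stated research question.

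**What to change.** Add one intervention-delivery cost line to the cost list, and state that it applies to the cost-consequence analysis, the cost-utility analysis and the long-term model. It should contain:

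- the monitor, annualised over its working life;
- staff time for training in home measurement;
- GP time for the first target and adjustment plan, only as far as it exceeds what is already recorded as a visit.

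State that GP appointments after self-adjustment are counted once, as visits. Vary the new line in the deterministic and probabilistic sensitivity analyses already planned. If a fuller document already costs these items, it is enough to say so in the list.

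The price is a few unit costs, available from the trial's own purchasing and staffing records, and a less favourable reported ratio. No visit, treatment or primary analysis changes.

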### Quality sub-study

Qualitative research techniques will seek to provide an in-depth understanding of the positive elements and areas of improvement related to self-titration and self-monitoring intervention. To this end, two meetings will be held, one with professionals (GPs and nurses) and one with patients, using the Nominal Group Technique (NGT). The NGT is a working methodology that establishes a framework for highly structured interaction that enables participation and equal consideration of the contributions of all members of the working group, and allows the identification of priorities, consensus and disagreement, solution generation and decision-making in an agile and objective manner [25].

## Discussion

The ADAMPA trial is a clinical research project that aims to improve the control of BP through training the patient for self-management of their hypertension. Hypertension is a risk factor of high prevalence that, even today, presents an unacceptable percentage of uncontrolled patients, according to the recommendations of the guidelines of clinical practice for BP control.

If the data from this trial show positive results, the study may contribute to a change of strategy in the treatment of hypertension, focusing on the patient as the main actor to achieve these objectives. Furthermore, this approach might contribute to the financial sustainability of the National Health Service.

## Abbreviations

BP: Blood pressure
DBP: Diastolic blood pressure
GP: General practitioner
mm Hg: Millimeter of mercury
NGT: Nominal Group Technique
PC: Primary care
PCC: Primary care centers
PDC: Proportion of days covered
SBP: Systolic blood pressure
SD: Standard deviation
SMBP: Self-measured blood pressure monitoring at home
TI: Therapeutic inertia
